### Data collection and study measures

Data collection is implemented in a secure database system designed at the UVa and is accessible only to limited internet-provided addresses. All data are kept on an encrypted server and participants are given a unique identifier. The minimum necessary number of research team members is given access to the data to help protect participant confidentiality. The measures are collected using mobile devices, allowing the research team to be flexible about where the data are collected and to adapt to patient and decision partner preferences regarding data collection. The research team monitors for participant and decision partner distress signs (e.g., fatigue, anxiety) and, to monitor participant burden on an ongoing basis, probes for feedback about participant reactions. Although depression and other signs of psychological stress are not considered an adverse event, if a patient or decision partner is determined to be at risk for depression—defined as a score of 16 or greater on the Center for Epidemiologic Studies Depression Scale [45]—they are referred to a mental health specialist. A member of the research team meets with each dyad (EUC and DI) for approximately 1 h at baseline and 20 min at each 3-month visit over the 9 months during which participants are enrolled in the study. All participants receive regular in-person or telephone contact by the CPN. This serves the purpose of helping participants access needed resources and keeps them engaged in the study to help retention. The mHealth delivery approach allows patients to make informed, quality decisions via decisional balance sheets, an audio cancer decision-making tutorial, and HRQL-PSY graphical summaries.

### Statistical analysis and power calculation

The main goal of this mixed-methods research is to test whether the decision support intervention is performing as hypothesized and warrants further research; thus, one-sided testing will be employed. The analysis plan assumes accrual (*N* = 158 dyads) for the quantitative portion of the study and a 15% dropout rate and assumes that the research team will have complete data on 134 dyads, providing approximately 89% power to detect an effect size of 0.5 for change in the main outcome measures for the DI group compared to no change in the EUC group using case-wise deletion. These calculations are informed by pilot data. Considering not all participants will be a dyad, and a smaller number will be single participants, it is unlikely that this would affect the power of the study. This will be reported in future dissemination materials once the study is completed.

For quantitative measures, descriptive analyses will be conducted as appropriate. Change in primary outcomes before and after the intervention will be assessed with analysis of covariance models that include the stratification factors (race and decision event), time, intervention arm, and a time-by-intervention-arm interaction. Additional analyses will assess whether the magnitude of change in primary outcome variables is similar between each member of the dyad using regression models that account for the correlation between each dyad and within participants over time. *Intention-to-treat* is defined as the analysis of all eligible patient-decision partner dyads by treatment as randomized, regardless of compliance with the intervention. Depending on the extent to which the data contain missing data, imputation will be considered for both the dyads and individual participants. Two methods will be used: (1) primary results will be based on an intention-to-treat analysis so that all eligible patients who entered the study will be included in the analyses regardless of compliance and (2) analyses will also include analysis of evaluable cases with more than 80% compliance (operationalized as completed all visits, all parts of the intervention but the home module, and had no other protocol violations) [48]. Using intention-to-treat analysis takes into consideration the bias of dropouts, but using both analyses provide more confidence in the conclusions of the trial if both analyses produce similar effects [48].

Qualitative data will be transcribed, coded into strips, and categorized by observed similarities [49]. The relationships of the categories will then be examined to construct themes, and the representativeness of these themes will be reviewed by the research team. Procedures will be employed to enhance validity, including modified member checking, dual coding, and peer/expert review.

Data quality will be audited regularly by the research team. No interim analyses will be performed. Any change to the protocol will be agreed upon between the investigators and filed with their respective IRB. This study has been deemed of minimal risk; therefore, a Data and Safety Monitoring Board has not been convened. Site visits will be conducted as necessary to ensure data and implementation quality. Adverse event reporting and monitoring is handled by the Principal Investigator and Institutional Review Board at each study site, and reviews will occur at least annually. The PI will report the event the IRB and Cancer Center Trials Office within 5 business days. All harms or adverse events (e.g., death unrelated to study intervention) are collected systematically and will be reported in trial publications, with consideration of maintaining patient privacy and confidentiality. Due to the unlikely event of harm related to this intervention, there are no plans to compensate participants for medical expenses, lost wages, disability, or discomfort. The charges for any medical treatment they receive will be billed to their insurance. The participants will be responsible for any amount of their insurance that is not covered.

No publication restrictions exist for this trial. All suggested topics for presentation or publication related to the trial will be sent to the PI of the study. There will be a discussion between PI and research team about the topic(s) for dissemination and where the dissemination items will be sent for review and potential acceptance. A query of those who are interested in substantially contributing to the presentation or publication will be made by the designated lead author. Assignments and contributions for the presentation or publication are made with the consideration of the authors’ expertise. There is no plan to utilize professional writers in the development of presentations or publications from this protocol.

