When a patient’s disease progresses to an advanced stage and the decision-making capacity wanes, decision partners often step into the role of proxy decision-maker for treatment-related decision-making for their loved ones [8]. Decision partners are ideal proxy decision-makers due to their proximity to the patient and knowledge of the patient’s values and preferences. The proxy decision-making process has been shown to be associated with negative outcomes for the decision partner, including stress, guilt, or depression [9, 10]. Decision partners may experience an immense amount of decision-making burden related to decision-making, particularly when patients have limited decision-making capacity for reasons such as brain metastases or cognitive deficits related to treatment. Studies [11–13] have noted the value of decision partners in helping to make decisions for terminally ill patients when they are most vulnerable [14].

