The Cancer Health Aid to Manage Preferences and Improve Outcomes through Navigation (CHAMPION) study intervention involves an interactive mHealth decision aid delivered by CPNs, and includes measures of health-related QoL throughout the course of the patient’s illness trajectory. The intervention has been pilot tested [39, 40] for advanced prostate cancer patients to enhance informed, shared decision making. In present study, the role of the CPN in the decision-making process will also be assessed. CHAMPION is designed to improve decision-making processes, match patients’ and decision partners’ preference to participate in treatment decisions, enhance patient-provider communication, and enrich psychosocial health-related quality of life (HRQOL-PSY) outcomes for patients and their decision partners. The primary aims of this study are to decrease decisional conflict/uncertainty, decrease decision regret, enhance HRQL-PSY, assess participation preferences in decision-making, and examine potential differences by race (African American versus White and Others) related to using the CHAMPION intervention. Because low decision-making involvement is thought to contribute to cancer-related health disparities, this novel intervention has the potential to positively impact the decision-making process for patients and their decision partners with the inclusion of the CPN, clarifying and supporting the treatment decision-making process.

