Decision partner	68	African American	Non-Hispanic	Public	Retired
**Sample case history:** Patient was diagnosed in 2009 with regionally metastatic prostate cancer, underwent surgery to remove the prostate and regional lymph nodes at that time. In 2017, the patient developed an elevated PSA and was diagnosed with bone metastases after imaging and began hormonal treatment. Six months later, the patient experiences bone pain and undergoes additional imaging that shows further metastases. He and his decision partner are approached by the research team to seek consent for participation in CHAMPION following a consultation visit to discuss treatment options with the oncologist. Informed consent is obtained from the patient and the decision partner. Baseline data are collected and the patient-decision partner dyad are enrolled and randomized to the DI arm. The CPN reviews the decision theory and the dyad is introduced to the balance sheet activity via the practice “telling others about cancer” decision. The dyad is sent home with the preloaded mp3 player. Ahead of their return visit, the CPN assesses the dyad’s concerns and conducts the single-event decision (starting, changing or stopping treatment). During the decision visit with the oncologist, there is structured time to discuss any concerns that arose during the balance sheet activity. Over the next 9 months, the CPN maintains regular contact and provides graphical summaries of the patient’s HRQL-PSY symptoms, as reported by both the patient and the decision partner.					

The target sample for this trial is 158 patient-decision partner dyads. Quota sampling will be applied to obtain a study sample of at least 40% African American. Although the intervention was not developed for primary use in the African American population, this target was chosen to facilitate the team’s ability to estimate the impact of the intervention in the African American population. Although prostate cancer has high incidence in African American men, minority participation can be low; thus, recruitment strategies are being applied that focus on African American participants.

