### Recruitment

Recruitment began in 2017 at UVa and JHU, and in 2019 at VCU. Participants are screened at each site using a variety of methods, including research team attendance at weekly clinical case discussions, manual chart review, and referrals from the clinical team. In this event-driven design, oncology clinic providers identify relevant events, such as the patient’s need to address starting, changing, or stopping treatment, and then refer eligible patient-decision partner dyads during weekly clinical trials meetings by teleconferences held at all institutions. In addition, the research teams attend weekly case discussions and discuss patients who may meet the eligibility criteria. The research team subsequently reviews these patients’ medical charts to determine eligibility. If a patient is eligible, the research team addresses the opportunity to participate in the study at the patient’s next clinical visit or over the telephone.

After confirming eligibility, the oncologist or another care provider introduces the study to the patient and decision partner. Patients experiencing serologic, radiographic, or symptom progression are contacted by the research team. The majority of patients and/or dyads are approached directly before or after their clinical visit with the medical oncologist. The research team reviews the study and, if the patient and/or the patient-decision partner dyad is willing, engages in an informed consent process to obtain oral consent or a signature from the patient and the decision partner, as approved by the facilities’ institutional review board (IRB). No data is planned to be used for further studies, which would constitute obtaining additional consent from current participants.

A previous version of the protocol required a decision partner for participation, but this requirement was removed after the study began, based on expert advice and research team discussion regarding the additional value of including patients without decision partners in the study. In the decision to include patients without decisional partners, there is a potential limitation in the analyses to compare between those patients who have decisional partners with those without decisional partners. We will plan to examine differences between dyads and single participants, particularly related to decisional conflict, regret, and quality of life.

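### One-sided testing is adopted without being limited to hypotheses that have a stated direction, and nothing says how a worsening under the decision intervention would be read

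*Protocol article*

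**What the plan says.** All places are in the protocol article.

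- **Sidedness.** Statistical analysis and power calculation: the goal is to learn whether the intervention performs as expected and "warrants further research; thus, one-sided testing will be employed". No alpha is given, and no outcome or comparison is exempted.
- **Power.** The same section plans on 134 complete dyads, "providing approximately 89% power to detect an effect size of 0.5 for change in the main outcome measures". The EUC arm is assumed not to change, and only complete cases are counted.
- **Directional aims.** The last paragraph of the Background aims to lower conflict, lower regret and raise psychosocial quality of life. Participation preference is only to be assessed.
- **Race.** The same list of primary aims includes a plan to "examine potential differences by race (African American versus White and Others", with no direction.
- **Participation preference.** Outcome variables lists it as the fourth primary outcome, measured by the Control Preference Scale.
- **Partner status.** Recruitment: "We will plan to examine differences between dyads and single participants".
- **Patient versus partner.** The statistical section asks whether the two members of a dyad change by a similar amount.
- **Psychological distress.** The Background reports that proxy decision-making is "associated with negative outcomes for the decision partner, including stress, guilt, or depression". Data collection and study measures does not class depression or other signs of psychological stress as adverse events. People above a depression-scale threshold are referred on.

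**The concern.** A one-sided test needs a direction fixed in advance. The article supplies one for three outcomes but words its testing rule without limits. Where no direction exists, the rule either cannot be applied or invites a choice of direction once the results are known, which doubles a nominal 5% error to 10% (2 × 5%).

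Participation preference is the clearest case. It is a primary outcome, and the Background speaks of matching people's preferred level of involvement, not of raising or lowering it. No tail can be called favourable.

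For the three directional outcomes the issue is different. In the formal test, a clear worsening under the decision intervention (DI) gives the same result as no effect. Because psychological distress falls outside the adverse-event definition, and the trial has no monitoring board or interim analysis, the arm comparison of these outcomes is the main formal place where a psychosocial worsening could show.

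**Working it through.** **Step 1. Does each planned comparison have a direction?**

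| Comparison | Direction stated? | One-sided test defined? |
|---|---|---|
| Conflict, DI vs enhanced usual care (EUC) | Yes, lower | Yes |
| Regret, DI vs EUC | Yes, lower | Yes |
| Psychosocial quality of life, DI vs EUC | Yes, higher | Yes |
| Participation preference (primary outcome) | No | No |
| Race (primary aim) | No | No |
| Dyad vs single participant | No | No |
| Patient vs partner | No, asks about similarity | No |

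**Step 2. Inputs.** 158 dyads and 15% dropout give 158 × 0.85 = 134.3, so 134 complete dyads. The effect size is 0.5 (SD set to 1). Alpha is not stated; 5% is assumed. The allocation ratio is not given; Study design, setting, and population says only that it favours DI, so a range is shown.

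**Step 3. Reproduce the stated 89%.** Power = Φ(0.5/SE − z), with SE = √(1/n_DI + 1/n_EUC).

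At 1:1, SE = √(1/67 + 1/67) = 0.173 and 0.5/SE = 2.894. One-sided 5%: Φ(2.894 − 1.645) = 89.4%. The noncentral t gives 89.1%.

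| DI:EUC | One-sided 5% (normal / t) | Two-sided 5% (normal / t) |
|---|---|---|
| 1:1 | 89.4% / 89.1% | 82.5% / 81.9% |
| 1.25:1 | 89.1% / 88.8% | 82.0% / 81.5% |
| 1.5:1 | 88.3% / 88.0% | 80.9% / 80.4% |
| 2:1 | 86.1% / 85.8% | 77.9% / 77.3% |
| 3:1 | 80.6% / 80.2% | 70.8% / 70.1% |

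The stated figure is reproduced by a one-sided 5% test at near-equal allocation. It does not fix alpha uniquely: one-sided 10% at 3:1 also gives 89.0%. That is a reason to state alpha.

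**Step 4. A true worsening of 0.5 SD under DI.**

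- One-sided 5%, 1:1: the test rejects with probability Φ(−2.894 − 1.645) = 0.000003, and then only in favour of benefit. It has no rejection region for harm.
- Two-sided 5%: the worsening is detected with about 82% power at 1:1 and 77% to 78% at 2:1 (right-hand column above).

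**Step 5. What an interval would add.** The half-width of a two-sided 95% interval is about 1.96 × 0.173 = 0.34 SD at 1:1. At 2:1, SE = √(1/89.3 + 1/44.7) = 0.183 and the half-width is 1.96 × 0.183 = 0.36 SD. An observed worsening larger than this puts the interval wholly on the harmful side, at no cost to the planned test.

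**The case against.** One-sided testing is defensible here. If the decision is whether to pursue the intervention further, no effect and harm both lead to stopping, and the article gives that reason. This stands, and the fix keeps one-sided tests for that purpose.

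The word that introduces the rule ties it to the hypothesised intervention effect. A reader might infer that the race and dyad-versus-single comparisons are to be tested in one direction. The documents do not support that: no sentence says so, both are only to be examined, and no test is named. What remains is a rule worded without limits beside aims it does not fit. Sidedness of secondary comparisons could be left to a fuller document, but participation preference is a primary outcome and race a primary aim.

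A reader might also infer that the trial could never report that DI makes things worse. That goes too far. Only the formal test is blind to it; arm estimates and descriptive results would show a worsening, and harms are collected and published. The last safeguard is weaker than it looks, because psychological distress is not counted as an adverse event.

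Finally, the Background's account of partner burden describes proxy decision-making in general, and the depression referral is a safeguard for anyone at risk. Neither is evidence that DI causes harm. They show only that a worsening is worth being able to recognise.

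**Conclusion.** The point holds in limited form. The one-sided rule is not restricted to the three outcomes with a stated direction. It cannot be applied as written to one primary outcome, participation preference, and does not suit the race, dyad-versus-single and patient-versus-partner comparisons. For the directional outcomes, the formal test treats a worsening as no effect, and the article does not say how one would be reported.

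This is not a claim that one-sided testing is wrong in itself, nor that the 89% is wrong. The figures in the working illustrate what the formal test leaves out. They rest on an assumed 5% alpha, 134 complete dyads and an allocation ratio the article does not give. This is a low-cost improvement that widens what the trial can conclude, not a defect in the planned directional comparison.

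**What to change.** In Statistical analysis and power calculation:

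1. State alpha. One-sided 5% is what the 89% implies at near-equal allocation.
2. Limit one-sided tests to DI versus EUC on conflict, regret and psychosocial quality of life, with the favourable direction named for each.
3. Report a two-sided 95% confidence interval for every arm difference, and say that an interval wholly on the harmful side is reported as a worsening.
4. Use two-sided 5% tests for participation preference and for the race, dyad-versus-single and patient-versus-partner comparisons.
5. Say that the one-sided test governs the decision on further research. A one-sided p-value between 0.025 and 0.05 will come with a 95% interval that includes zero.

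**Cost.** Wording only. The 89% is unchanged while the directional primary tests stay one-sided. Making those two-sided as well is not needed for this point and would not be free: power would be about 82% at 1:1 or 77% to 78% at 2:1. Keeping 89% would need 164 complete dyads (164/0.85, so 193 enrolled) at 1:1, or 183 complete (183/0.85, so 216 enrolled) at 2:1, against the planned 134 and 158.

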7. **Structured time/data sharing** (i.e., balance sheet and HRQL-PSY graphical summaries) **with oncology providers** to support the oncology provider’s interactions with the patient-decision partner dyad and facilitate decisions.	

The decision-making tutorial is initially presented with a practice decision balance sheet (“telling others about cancer”) as the first decision and, in brief, as a “booster” for subsequent decisions [40]. The practice decision is meant to be less consequential and threatening than the three single-event decisions, allowing participants to practice decision skills. Once patients receive initial treatment options from their providers, they undertake values clarification using the balance sheets with the CPN before the next clinic visit. Structured time with the CPN and enhanced communication with oncology providers related to the decision process is an important intervention component, promoting multidisciplinary collaboration to address issues related to disease progression. Through this interactive process, the mHealth decision aid emphasizes informed, shared decision-making for patients, decision partners, the CPN, and oncologist through values clarification and decision preference. Reports of intervention adherence are collected from participants and the research team. The mHealth decision aid delivery approach allows patients to make informed, quality decisions by cancer care educational audio files, by immediate and over time HRQL-PSY graphical summaries, and by decision balance sheets, while including a support structure with the decision partner, CPN, and oncologist.

A participant has the option to withdraw from the study if they no longer wish to participate in the study, or if a patient dies during the study that is not related to the protocol, then he will be withdrawn from the study. Standard of care is allowed as part of the intervention, which includes pamphlets and brochures of the anti-cancer treatment that is provided by the healthcare provider, but oral, written, or recorded materials related to decision making are not permitted. There will be no blinding to group assignments with the exception of the data analysts. We learned from pilot studies that having CPNs dedicated to either the decision intervention group or enhanced usual care group alleviates treatment diffusion issues.

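### The terms listed for the primary ANCOVA do not fit the four primary outcomes: no baseline score is named, and within-person correlation is mentioned only for additional analyses

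*Protocol article*

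**What the plan says.** In the Protocol article, under Statistical analysis and power calculation, change in the primary outcomes is to be assessed by analysis of covariance. The terms given are the stratification factors and what follows: "race and decision event), time, intervention arm, and a time-by-intervention-arm interaction". The baseline score is not among them. The next sentence turns to additional analyses, which compare the two members of the dyad, and says these are done "using regression models that account for the correlation between each dyad and within participants over time". Correlation is mentioned nowhere else in the section.

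Table 3 (Outcome variables) gives the data structure:

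- Decisional conflict: change from baseline, measured at baseline and 9 months.
- Decision regret: value at 9 months.
- Health-related quality of life and decision-making participation: change from baseline at 3, 6 and 9 months.

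The power statement in the same section says "thus, one-sided testing will be employed", allows for "a 15% dropout rate" and expects "complete data on 134 dyads". It claims about 89% power for an effect size of 0.5 on change. No alpha is stated. Under Study design, setting, and population, allocation is weighted towards the decision intervention (DI) arm, but no ratio is given.

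**The concern.** One list of terms is applied to four outcomes with three different structures.

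- **Decision regret** is measured once, so time and time-by-arm cannot be estimated.
- **Decisional conflict** gives one change value per person, so the same holds. The time terms can be fitted only if the raw baseline and 9-month scores both enter as responses, which gives two correlated rows per person.
- **Quality of life and participation preference** give three correlated rows per person.

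Wherever a person contributes more than one row, the standard error (SE) depends on how the correlation is handled. The article raises that subject only for a secondary question. It also does not say which coefficient is the primary test, and the error from ignoring correlation has opposite signs for different coefficients. A true effect could be missed or a false one declared. Separately, a model without the baseline score as a covariate gives up precision that data already collected would supply.

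**Working it through.** **Inputs.** From the article: 158 dyads, 15% dropout, 134 complete dyads, effect size 0.5 on change, one-sided testing, more DI than enhanced usual care dyads. Assumed: one-sided alpha 0.05 (z = 1.645), effect measured in SDs of change, allocation from 1:1 to 1.5:1, equal variances at each time, and correlation ρ of 0.3, 0.5 or 0.7.

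**1. The plan's own figure.** 158 × 0.85 = 134.3, so 134 reproduces. For a two-group comparison of one change value per dyad, power = Φ(0.5/s − 1.645), where s = √(1/n₁ + 1/n₂).

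- 1:1 (67 and 67): s = 0.1728, 0.5/s = 2.894, power 89.4%.
- 1.5:1 (80.4 and 53.6): s = 0.1763, 0.5/s = 2.836, power 88.3%.
- 2:1: 86.1%, which no longer matches.
- One-sided 0.025 at 1:1: 82.5%, which does not match.

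The stated 89% is therefore sound for a change-score comparison at one-sided 0.05. That is not a model with time and time-by-arm terms.

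**2. Baseline and 9-month scores stacked as independent, time-by-arm tested.** The model takes the variance of a difference as 2σ²; the true value is 2σ²(1 − ρ). The SE is overstated by k = 1/√(1 − ρ). True size = 1 − Φ(1.645k). Power = Φ(0.5/s − 1.645k).

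| ρ | k | True type I error | Power, 1:1 | Power, 1.5:1 |
|---|---|---|---|---|
| 0.3 | 1.20 | 2.5% | 82.3% | 80.8% |
| 0.5 | 1.41 | 1.0% | 71.5% | 69.5% |
| 0.7 | 1.83 | 0.1% | 45.7% | 43.3% |

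A simulation of 4,000 trials per setting (134 dyads, 60:40) gave power of 81%, 69% and 44%.

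**3. Three change scores treated as independent, arm effect averaged over visits tested.** Here ρ is the correlation among the change scores. The true variance of a person's mean is (1 + 2ρ)/3 of the single-visit variance; the model uses 1/3. The SE is understated by the factor 1/√(1 + 2ρ) = 0.79, 0.71, 0.65. True type I error = 1 − Φ(1.645 × factor) = 9.7%, 12.2%, 14.4%, against a nominal 5%.

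An arm contrast at a single visit has an SE ratio of about 1, so it is largely unaffected. The coefficient chosen decides the direction and size of the error.

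**4. Baseline as covariate.** The variance ratio of baseline-adjusted ANCOVA to change score is (1 − ρ²)/[2(1 − ρ)] = (1 + ρ)/2 = 0.65, 0.75, 0.85. Power = Φ(0.5/(s√ratio) − 1.645). At 1:1 this is 97.4%, 95.5% and 93.2%. The simulation at 60:40 gave 96%, 95% and 92%.

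**The case against.** The strongest reply is that the error is not written down. The article names terms the models include; it does not say that the list is complete or that observations are treated as independent. A condensed article may leave the covariance structure to the full plan, and the next sentence shows that the authors know about correlation within persons and dyads. Analysis of covariance of change may also be shorthand for baseline adjustment. All of this stands, so the SE result must be stated conditionally. A reader might infer that the primary SE is wrong, or that power is certainly lost; the document supports neither. An unadjusted change-score comparison is valid under randomisation, and the 89% reproduces on that basis, so baseline adjustment is a gain in efficiency and not the repair of a bias.

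The reply does not remove the mismatch with Table 3. Time terms cannot be estimated for an outcome measured once, or for a single change value, whatever the covariance structure.

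A reader might also infer that omitting site or navigator is an error. The article says "Recruitment began in 2017 at UVa and JHU, and in 2019 at VCU", and that "having CPNs dedicated to either the decision intervention group or enhanced usual care group alleviates treatment diffusion issues". But randomisation was stratified by race and decision event only, and the model carries both, so design and analysis agree. Nothing in the article shows that leaving site out makes the SE of the arm effect wrong. The African American shares reported for the three centres describe catchments or centre patients, not trial participants. Navigators dedicated to one arm raise a separate clustering question that a site term would not settle.

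**Conclusion.** The point holds in two parts. First, without any assumption, the listed terms cannot be fitted to decision regret, nor to decisional conflict in the change metric of Table 3. Second, and conditionally, if the model were fitted as listed with rows treated as independent, the time-by-arm test on stacked baseline and 9-month scores would be conservative, while an arm effect averaged over three change scores would be anti-conservative, with the sizes shown above.

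The figures rest on the assumed correlations, alpha and allocation, none of which the article gives. The stated power is not itself in error; it belongs to a simpler analysis than the one described. Because the candidate models differ so much in error rate and power, the choice should be fixed in writing before results by arm are seen.

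**What to change.** Replace the single list of terms with one model per outcome, and name the coefficient tested in each:

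- **Decisional conflict:** ANCOVA of the 9-month score on arm, baseline score, race and decision event; test the arm coefficient.
- **Decision regret:** 9-month comparison of arms adjusted for race and decision event, with no time terms; test the arm coefficient.
- **HRQL-PSY and participation preference:** repeated-measures model on the 3-, 6- and 9-month scores with baseline score, baseline-by-time, arm, time, arm-by-time, race, decision event and a within-participant covariance, plus a dyad-level covariance if both members are modelled. State whether the primary contrast is the arm difference at 9 months or the average over visits.

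State the one-sided alpha and the allocation ratio beside the power figure. If the full analysis plan already contains these models, a sentence saying so is enough.

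The cost is a little more wording and one or a few degrees of freedom. Baseline measures are taken before randomisation, so no new data are needed. The repeated-measures model presumes that both arms supply scores at 3 and 6 months; the sentence introducing Table 3 mentions the 3-monthly HRQL-PSY only for DI participants, so this should be confirmed. Site adjustment and a sensitivity analysis by navigator are optional additions and correct no error; the latter needs navigator identity, which the article does not say is recorded.
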